## Abstract

**Background:**

Suboptimal treatment of hypertension remains a widespread problem, particularly among minorities and socioeconomically disadvantaged groups. We present a health system–based intervention with diverse patient populations using readily available smartphone technology. This intervention is designed to empower patients and create partnerships between patients and their provider team to promote hypertension control.

**Objective:**

The mGlide randomized controlled trial is a National Institutes of Health–funded study, evaluating whether a mobile health (mHealth)-based intervention that is an active partnership between interprofessional health care teams and patients results in better hypertension control rates than a state-of-clinical care comparison.

**Methods:**

We are recruiting 450 participants including stroke survivors and primary care patients with elevated cardiovascular disease risk from diverse health systems. These systems include an acute stroke service (n=100), an academic medical center (n=150), and community medical centers including Federally Qualified Health Centers serving low-income and minority (Latino, Hmong, African American, Somali) patients (n=200). The primary aim tests the clinical effectiveness of the 6-month mHealth intervention versus standard of care. Secondary aims evaluate sustained hypertension control rates at 12 months; describe provider experiences of system usability and satisfaction; examine patient experiences, including medication adherence and medication use self-efficacy, self-rated health and quality of life, and adverse event rates; and complete a cost-effectiveness analysis.

**Results:**

To date, we have randomized 107 participants (54 intervention, 53 control).

**Conclusions:**

This study will provide evidence for whether a readily available mHealth care model is better than state-of-clinical care for bridging the guideline-to-practice gap in hypertension treatment in health systems serving diverse patient populations.

**Trial Registration:**

Clinicaltrials.gov NCT03612271; https://clinicaltrials.gov/ct2/show/NCT03612271

**International Registered Report Identifier (IRRID):**

DERR1-10.2196/25424

## Introduction

Hypertension (HTN), a major risk factor for strokes and heart attacks, is also a significant comorbidity in severe COVID-19 infections [1-3]. Unfortunately, of the estimated 86 million US adults with HTN, 46% (~40 million) have poorly controlled or uncontrolled HTN [4]. Despite widespread recognition of the health risks of HTN, suboptimal treatment of HTN remains a pernicious problem and is marked by disparities [4,5]. Rates of HTN control are worse among racial and ethnic minorities and socioeconomically disadvantaged groups, who experience a disproportionate burden of cardiovascular disease (CVD) and poor health outcomes [4,5]. According to the 2017-2018 National Health and Nutrition Exam Survey, rates of controlled HTN in Hispanic adults (36.8%) were substantially lower than in non-Hispanic white adults (45.2%) [6]. HTN is undertreated even among stroke survivors who are at significantly increased risk of recurrent stroke [7]. Many factors have been associated with suboptimal HTN control including gaps in health services, lower socioeconomic status, and limited self-care [8-10].

Self-measured blood pressure monitoring (SMBP), an aspect of self-care, is effective in lowering blood pressure (BP) and improving HTN control [11]. SMBP is recommended in guidelines on the care of patients with HTN including the Eighth Joint National Committee [1] and the American College of Cardiology [12,13]. It was also endorsed in a joint policy statement by the American Heart Association (AHA) and American Medical Association as a result of increasing utilization of telehealth visits in the COVID-19 pandemic [14].

Mobile health (mHealth) technology has emerged as an innovative way to facilitate SMBP [15,16]. Our prior pilot study with stroke survivors found that SMBP utilizing mHealth improved rates of HTN control [17]. In a randomized controlled trial (RCT), we compared usual care versus an mHealth-based model of HTN care that included automated wireless transmission of BP data to the provider team, including a clinical pharmacist, who could make responsive medication adjustments. The mHealth care model was feasible and acceptable to stroke survivors and was highly effective: 89% of participants in the mHealth group versus 58% in the usual care group (*P*=.015) had their BP controlled at 3 months postrandomization. However, the generalizability of our results was limited as all the participants were stroke survivors and the majority of participants were English-speaking Caucasians, which is typical of many published studies [15]. To the best of our knowledge, there are no published studies that evaluate mHealth-based HTN care in Hmong patients.

To address these gaps, we designed an RCT, called mGlide, to evaluate whether an mHealth-based active partnership between health care teams and patients results in better HTN control than a state-of-clinical care comparison (usual care) for stroke survivors and persons at elevated risk of CVD. We are particularly interested in addressing disparities in HTN control in vulnerable patient populations in our region. Thus, our recruitment sites include federally qualified health centers (FQHCs) that predominantly serve low-income racial or ethnic minorities and immigrants, including lower socioeconomic groups and African American, Hmong, Somali, and Latino patients. The primary study aim tests the clinical effectiveness of the 6-month intervention vs usual clinical care. Secondary aims evaluate sustained HTN control rates at 12 months; describe provider experiences of system usability and satisfaction; examine patient experiences, including medication adherence and medication use self-efficacy, self-rated health and quality of life, and adverse event rates; and complete a cost-effectiveness analysis. The mGlide RCT began in late 2018, with recruitment initiated in March 2019. Our purpose in this article is to describe the design and rationale of the mGlide RCT study.

## Methods

### Study Design

mGlide is a National Institutes of Health–funded, investigator-initiated, 12-month, 2-arm RCT evaluating HTN control rates between the study intervention and clinical comparison groups. We use a PROBE (Prospective Randomized Open Blinded End-point) design. We are recruiting a total of 450 patients with uncontrolled hypertension who are either stroke survivors or primary care patients at elevated risk of CVD from the metropolitan area of Minneapolis and Saint Paul, Minnesota. The recruitment window is between March 2019 and December 2022. Individual participants are randomized to either the multilevel mGlide intervention (target n=225) or to state-of-clinical care (target n=225) for a 6-month intervention period, followed by a 6-month observation period. A baseline BP assessment and 2 follow-up BP assessments (at 6 months and 12 months postrandomization) are completed for each participant.

Eligibility criteria are shown in Textbox 1 and in the CONSORT flow diagram (Figure 1). The University of Minnesota Institutional Review Board (IRB) approved the study protocol, and all participants provide written, informed consent.

mGlide randomized controlled trial eligibility criteria.
**Inclusion criteria**
Aged 18-85 yearsEstablished medical diagnosis of hypertension (HTN)Uncontrolled HTN during screening defined as:Systolic blood pressure (SBP) >140 mm Hg at last 2 clinic visits in the 6 months prior to the screening date
orIf a patient is discharged from the hospital in the 6 months prior to screening and does not have 2 clinic visits after hospital discharge, at least 1 SBP in last 2 hospital days >140 mm Hg
orIf only 1 office visit and no hospitalization in last 6 months, then a single SBP in the system >150 mm Hg and SBP >140 mm Hg at an invited pre-enrollment screening visitBe at high cardiovascular disease (CVD) or stroke risk, defined as:History of ischemic stroke or intraparenchymal hemorrhage
orHistory of established CVD disease (coronary artery disease, peripheral vascular disease)
orElevated risk of stroke or CVD events as defined by the American Heart Association (AHA)/American College of Cardiology (ACC) guideline on risk stratification ≥7.5% over 10 years if ≥40 years old and ≥10% nonpooled risk calculation if <40 years oldEnglish, Spanish, Hmong, or Somali speakingHave a smartphone or mobile device (eg, iPad) that can transmit blood pressure (BP) from the BP monitor; iOS and Android compatible (iOS 7 or higher: iPhone 4 or higher, iPod touch 5th generation or higher, iPad 2nd generation or higher; Android 4.0 or higher)Capable and willing to comply with the entire study protocolAble to give voluntary written informed consent
**Exclusion criteria**
Severe comorbid illness including end-stage kidney disease, end-stage liver disease, and life expectancy <1 year, or if medical complexity of the patient precludes clinical trial participationActive illicit drug use (eg, cocaine, methamphetamines, opioids, phencyclidine)Unable to complete study tasks, including are homeless, will leave the country, or will relocate in the next 12 monthsSerious psychiatric illness that could interfere with treatment, assessment, or compliance including significant delusional disorders such as schizophrenia and bipolar illnessUnable or unwilling to give consent

**Figure 1 figure1:**
[figure not shown]
mGlide CONSORT diagram. EMR: electronic medical record.

### Study Setting and Recruitment

The study is conducted by the University of Minnesota, a large urban university in the upper Midwest in the United States. Study participants are community-dwelling residents within our 7-county metropolitan area recruited from (1) a large academic health system (Fairview Health System) with a stroke service and primary care clinics; (2) university-affiliated, community-based, primary care clinics serving low-income participants and minorities (University of Minnesota Physicians clinics); and (3) 2 FQHCs: Minnesota Community Care, the largest FQHC in Minnesota, and Neighborhood Health Source, serving low-income people from ethnically diverse communities. Details are in Table 1.

**Table 1 table1:** Planned enrollment (N=450).

Site	Number of participants	Description of recruited participants
Fairview stroke service	100	Stroke survivors
Fairview primary care clinics	150	Elevated CVD^a^ risk
UMP^b^ primary care clinics	125	Elevated CVD risk; low income; diverse; minority
FQHC^c^ clinics (MnCC^d^, NHS^e^)	75	Elevated CVD risk; low income; diverse; minority

^a^CVD: cardiovascular disease.

^b^UMP: University of Minnesota Physicians.

^c^FQHC: federally qualified health centers.

^d^MnCC: Minnesota Community Care.

^e^NHS: Neighborhood Health Source.

Eligible stroke survivors are identified from the Fairview acute stroke service and the acute rehabilitation unit. Primary care patients are identified by electronic medical record queries using the inclusion and exclusion criteria in Textbox 1. Patients who have “opted out” of research are not included in the electronic medical record query (~5% of all patients). Eligible participants are mailed a study brochure and are subsequently contacted by phone. Those who express interest undergo a second screening for availability of a smartphone or mobile device and are invited for a baseline enrollment visit.

### Visit Schedule and Assessments

Each participant completes a total of 3 visits: baseline visit and 2 follow-up visits at 6 months and 12 months postrandomization. The baseline visit includes informed consent in the participant’s language, randomization into one of the 2 study arms, participant education about HTN and BP control, baseline BP measurement using a protocol [18,19], and baseline surveys. The 2 follow-up visits include assessments of the primary and secondary study outcomes. In addition, team members call participants monthly (months 1-5) and bimonthly (months 8 and 10) to identify adverse events and address any challenges. Data collection details are presented in Table 2.

**Table 2 table2:** mGlide randomized controlled trial visit schedule and assessments at baseline and follow-up.

Measures		Baseline	6-month follow-up	12-month follow-up
Demographic information		x	N/A^a^	N/A
Medical history		x	N/A	N/A
Health behaviors (smoking, physical activity, diet, sleep)		x	N/A	N/A
Health insurance		x	N/A	N/A
Blood pressure		x	x	x
**Patient-reported outcomes**				
	Health care experiences (CAHPS^b^ adult survey)	x	x	x
	Hill-Bone Medication Adherence Scale (HB-MAS)	x	x	x
	Medication and Self-Efficacy Scale - Revised (MASES-R)	x	x	x
	Patient Activation Measure (PAM-10)	x	x	x
	Health care utilization	x	x	x
	Self-reported health status (EQ-5D-3L)	x	x	x
	Technology usability (Marshfield System Usability Survey)	N/A	x	N/A

^a^N/A: Not applicable.

^b^CAHPS: Consumer Assessment of Healthcare Providers and Systems.

### Special Considerations for Recruitment

University of Minnesota researchers and community researchers from Hmong and Latino communities co-developed the informed consent and surveys in English. Subsequently, community researchers translated all participant-facing documents into Hmong, Spanish, and Somali. Each participant invited to a baseline enrollment visit works with a team member who speaks their language (Hmong, Spanish, Somali, or English).

### Randomization

Eligible and consented participants are randomized 1:1 to either an intervention mGlide arm or a state-of-clinical-care comparison arm. The randomization uses a site-specific randomization schedule and is stratified across the 4 participant groups discussed in Table 1. Randomization schedules follow from permuted blocks with randomly varying sizes to ensure approximate balance between the 2 study arms in each stratum across the trial while reducing predictability of the assignments.

### Interventions

#### mGlide

The mGlide intervention has 3 components (Table 3): participant education on the importance of HTN control, training on SMBP and wireless transmission of BP, and responsive antihypertensive medication adjustment by the pharmacist-provider team.

Each participant receives education on the importance of HTN control via an IRB-approved educational video available in English, Spanish, and Hmong. We previously developed this video through a community-engagement process led by community researchers from the Hmong and Latino communities. The study team member then trains the participant on SMBP [18] using a wireless BP monitor provided by the study and a smartphone (participant’s own phone or mobile device such as iPad). The intervention participants are requested to self-monitor their BP daily with specific guidance on timing and proper technique based on the AHA recommendations [18]. The self-monitored BP is automatically transmitted to a provider REDCap database and is used for responsive antihypertensive medication adjustment. The participant BP transmission is automated and facilitated by the participant’s mobile device via an app. Pharmacist teams at each clinic location access the BP data via a web-based user interface that identifies patients whose readings were out of bounds during the prior week. This user interface creates efficiencies for pharmacists reviewing the data and was developed to avoid information overload for pharmacists. Pharmacists adjust medications based on collaborative practice agreements with primary care providers (PCP) and mGlide protocols. Pharmacists adjust medications and communicate with the patient and their PCP as often as every 2 weeks or as needed to reach the BP goal.

**Table 3 table3:** Components of mGlide intervention delivered to participants.

Component	Intervention	Comparison
Education on importance of hypertension control	Yes	Yes
Training in blood pressure self-monitoring	Yes	Yes
Daily self-monitoring	Requested	Encouraged
Automated wireless blood pressure transmission via mobile device	Yes	No
Responsive medication adjustment by pharmacy	Yes	No
Primary care follow-up as usual	Yes	Yes

Our intervention is a multilevel model with a 3-member team: frontline research team member who educates the participant and trains them on self-monitoring of BP, pharmacist who provides responsive HTN management, and PCP. This team communicates via the electronic medical record as part of clinical care.

#### State-of-Clinical Care Comparison

Each study participant randomized to the clinical care comparison group receives the same education as intervention participants on the importance of HTN control via the IRB-approved educational video. The comparison group participants receive a digital BP monitor and are trained on BP self-monitoring with proper technique. Participants are encouraged to measure their BP daily and follow up with their PCP regarding their BP, as requested by the PCP as part of their clinical care. Participants, PCPs, and clinic teams are responsible for communicating as they would in usual clinical care. In other words, there is no predetermined follow-up schedule with the PCP specified by the study, and there is no automatic transmission of participant BP readings to providers; rather, participants are responsible for sharing their BP and working with their care team to manage their BP.

### Analysis

#### Outcomes

The main outcome will be the rate of HTN control at 6 months; the primary outcome will be defined as a binary indicator of uncontrolled HTN or death versus controlled HTN at 6 months. The BP is measured in-person in the clinical research center by a trained staff member who is blind to the patient’s assignment. The BP is measured 4 times using a standard digital monitor using proper technique, and the average of the last 3 BP measurements denotes the BP outcome. HTN control is defined as systolic blood pressure (SBP) <140 mm Hg, which is consistent with American College of Physicians, American Association of Family Physicians, and AHA primary and secondary stroke prevention guidelines [12,13,20]. The 2017 American College of Cardiology/AHA guidelines recommend a SBP goal of <130 mm Hg. The HTN treatment goals and target BP were discussed with the PCPs and clinical pharmacists at all sites prior to study recruitment. Everyone agreed to target a SBP goal of <140 mm Hg for intervention arm participants and requested that lower SBP goals be left to the discretion of the study pharmacists managing the patient. Study pharmacists have access to patient medical records. At 12 months, the BP outcome is assessed in the same manner as at 6 months. This allows the assessment of the secondary outcome of uncontrolled HTN or death versus controlled HTN at 12 months. Additional secondary outcomes include patient-reported medication adherence, medication use self-efficacy, self-reported health status, and quality of life that we assess with validated questionnaires at each of the 3 study visits. We ascertain participant adverse events and health care utilization during monthly phone calls during the first 6 months of the study and bimonthly in months 7-11. We also assess care providers’ experience of the mGlide system usability.

#### Power and Sample Size

Sample size was calculated to address outcomes of failure to achieve HTN control or death at 6 months and 12 months after randomization. We based sample size calculations on (1) reported 1-year stroke survivor mortality rate of 4% [21] and assuming similar mortality among primary care participants with elevated CVD risk, (2) pilot results that showed a primary outcome rate of HTN control or death at 6 months of 15% in the intervention and 50% in the comparison groups [17], and (3) a 20% attrition rate. We identified that a sample size of 450 would provide at least 85% power, with an alpha of .05 to detect a 15% effect size. We planned for a more modest intervention effect size than achieved in our pilot results due to the longer period of observation and more diverse health systems and patient populations when compared to the pilot study. Similarly, while the loss to follow-up in the pilot study was very modest at 4%, we planned for a 20% attrition rate due to the economically stressed primary care population in our low-resource health systems. Nationally reported rates of uncontrolled HTN in stroke survivors are ~50% [7]. FQHC primary care rates of uncontrolled HTN are ~38%-40% [22]. Our sample size will allow valid subgroup analysis among the subgroup of primary care patients in all low-income sites (n=200) and the stroke survivor subgroup (n=100).

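### The power claim of at least 85% names no comparison rate and falls to about 82-83% at the listed 50%; the pilot input is mislabelled and unreconciled

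*Protocol article*

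**What the plan says.** The Power and Sample Size section of the protocol article lists three numbered inputs:

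- a 1-year mortality of 4%;
- pilot results, described as a "primary outcome rate of HTN control or death at 6 months of 15% in the intervention and 50% in the comparison groups";
- 20% attrition.

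It then concludes that "a sample size of 450 would provide at least 85% power, with an alpha of .05 to detect a 15% effect size". The planned effect was deliberately set smaller than the pilot effect. Later the section cites uncontrolled rates of about 50% in stroke survivors and about 38%-40% in FQHC primary care. It does not say which rate the 15% is subtracted from.

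The Randomization section says "Eligible and consented participants are randomized 1:1", and Study Design sets a target of 225 per arm.

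The Introduction reports the same pilot, under the same reference number, differently: "89% of participants in the mHealth group versus 58% in the usual care group" "had their BP controlled at 3 months postrandomization" (a P value stands between these two parts in the original).

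**The concern.** A claim of at least 85% is a lower bound, so it should hold at every comparison rate the section offers as a basis. The natural first check uses the one comparison rate among the numbered inputs, 50%, and there the claim fails. A reader cannot tell what the 85% refers to, or how far power depends on the comparison rate the trial meets.

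The pilot input has two further defects. Read literally, its label says that 15% of intervention participants and 50% of comparison participants reached control or died, which would mean the intervention did harm. And neither the values nor the time point match the pilot result in the Introduction.

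**Working it through.** **Inputs.** N = 450, 1:1, so 225 per arm (Study Design, Randomization). Attrition is 20%: 450 × 0.8 = 360 evaluable, n = 180 per arm. Alpha is .05; sidedness is not stated, and I take it as two-sided because Planned Analysis asks whether the odds differ. I read the 15% effect size as an absolute difference, d = 0.15.

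**Formulas.** For comparison rate p1, intervention rate p2 = p1 − 0.15 and p̄ = (p1 + p2)/2:

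- s0 = √[2p̄(1 − p̄)/n] and s1 = √{[p1(1 − p1) + p2(1 − p2)]/n}
- pooled power = Φ[(d − 1.960·s0)/s1]
- unpooled power = Φ[d/s1 − 1.960]

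**Where the stated figure reproduces: 42% versus 27%.** s0 = 0.0501 and s1 = 0.0495. Pooled: Φ(1.047) = 85.2%. Unpooled: Φ(1.072) = 85.8%. Solving for 85% gives 179 per arm, 358 in total, and 358/0.8 = 448 randomised, close to 450.

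**At the listed 50%: 50% versus 35%.** s0 = √(2 × 0.425 × 0.575/180) = 0.0521 and s1 = √[(0.25 + 0.2275)/180] = 0.0515. Pooled: Φ(0.929) = 82.4%. Unpooled: Φ(0.952) = 83.0%. Other methods agree: arcsine 82.4%, exact 82.1%, simulated four-stratum Cochran-Mantel-Haenszel 82.2%, continuity-corrected 79.4%.

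**Across comparison rates (180 per arm, two-sided, pooled).**

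| Comparison rate | Power |
|---|---|
| 38% | 87.4% |
| 40% | 86.3% |
| 42% | 85.2% |
| 45% | 83.9% |
| 50% | 82.4% |
| 57.5% (minimum) | 81.5% |

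**What would give 85% at 50% versus 35%.** It needs 194 evaluable per arm, 388 in total, so 388/0.8 = 485 randomised. With 450 randomised, attrition could be at most 1 − 388/450 = 13.8%.

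**Other routes to 85% at 50%.** Ignoring attrition (225 per arm) gives 89.9%, and a one-sided test gives 89.4%. Neither fits the plan as written. Taking attrition as 450/1.2, or 187.5 per arm, gives 83.9%, still below 85%.

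**Pilot figures side by side.**

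| Source | Time point | Intervention | Comparison | Gap |
|---|---|---|---|---|
| Introduction, not controlled (100 − 89; 100 − 58) | 3 months | 11% | 42% | 31 points |
| Power and Sample Size, composite with death | 6 months | 15% | 50% | 35 points |

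The label in the second source conflicts with the Outcomes section, which counts uncontrolled HTN or death as the event. It also conflicts with the opening sentence of Power and Sample Size, which speaks of failure to achieve control.

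**The case against.** The strongest reply is that the article never says the 15 points start from 50%. The planned effect departs from the pilot on purpose, and only 100 of the 450 participants are stroke survivors. If 100 are assumed at 50% and the other 350 at 39%, the comparison rate is (50 + 136.5)/450 = 41.4% and power is 85.5%. The claim also reproduces at the pilot's 42%. This stands. A reader might infer that the 85% is an arithmetic error, and the documents do not support that: it may have been computed correctly at a lower rate. It does not rescue the words *at least*, because the section cites about 50% twice. The FQHC figure describes clinic patients, whereas enrolment requires raised SBP at screening, so nothing in the article establishes it as the trial's comparison rate.

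A reader might also add the 4% mortality to 42%, giving 46% versus 31% and 83.6-84.1% power, and conclude that the claim fails there too. That is not established for the primary endpoint: 4% is a 1-year rate, the endpoint is at 6 months, and the article does not say whether the pilot's 42% already includes deaths.

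On the pilot, the two sets of figures may describe different endpoints or time points from one source. They are therefore unreconciled rather than strictly contradictory, and one cannot say from the article which set is right. The label is probably a dropped word, and the Outcomes section defines the endpoint correctly, but as printed it reverses the result.

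Finally, the gap is small, the pilot rates do not set the 15-point effect, and multiple imputation with covariates may recover some information that a completer-only calculation omits. All this limits the weight of the point but does not remove it.

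**Conclusion.** The point holds as a defect of specification and wording. With 180 evaluable per arm, a two-sided .05 test and a 15-point absolute difference, power is about 82-83% at a comparison rate of 50%. It is 85-86% at 42% and 86-87% at 40%. The stated lower bound is met only up to about 42%, so it does not cover the rates the section itself gives. The shortfall at 50% is 2-3 points, equivalent to 485 − 450 = 35 more participants. The result rests on the two-sided and absolute readings and on attrition being applied as a 20% loss.

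The pilot label is wrong as printed, and the pilot's values and time point are not reconciled between the two sections. Neither defect changes the endpoint, the planned test or the case for 450.

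**What to change.** Keep N = 450 and amend the Power and Sample Size section:

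1. State the comparison rate, two-sided alpha .05 (if that is what was used), an absolute difference of 15 percentage points, and 360 evaluable (180 per arm) after 20% attrition.
2. Replace the claim of at least 85% with about 82-83% for 50% versus 35% and about 85% for 42% versus 27%.
3. Correct the pilot outcome label to uncontrolled HTN or death.
4. Reconcile the pilot values and time point with the Introduction, or explain how 15% and 50% at 6 months were derived.

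The cost is wording only. The stated power becomes slightly less favourable, and no design or analysis step changes.
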